# “Watch Me Grow- Electronic (WMG-E)” surveillance approach to identify and address child development, parental mental health, and psychosocial needs: study protocol

**DOI:** 10.1186/s12913-021-07243-0

**Published:** 2021-11-17

**Keywords:** Child development, Parent mental health, Psychosocial needs, Screening, Developmental surveillance, Service navigation, Virtual care, Digital solution, Online health service, Electronic platform

## Abstract

**Background:**

The COVID-19 pandemic and the associated economic recession has increased parental psychosocial stress and mental health challenges. This has adversely impacted child development and wellbeing, particularly for children from priority populations (culturally and linguistically diverse (CALD) and rural/regional communities) who are at an already increased risk of health inequality. The increased mental health and psychosocial needs were compounded by the closure of in-person preventive and health promotion programs resulting in health organisations embracing technology and online services. Watch Me Grow- Electronic (WMG-E) – developmental surveillance platform- exemplifies one such service.

WMG-E was developed to monitor child development and guide parents towards more detailed assessments when risk is identified. This Randomised Controlled Trial (RCT) aims to expand WMG-E as a digital navigation tool by also incorporating parents’ mental health and psychosocial needs. Children and families needing additional assessments and supports will be electronically directed to relevant resources in the ‘care-as-usual’ group. In contrast, the intervention group will receive continuity of care, with additional in-person assessment and ‘warm hand over’ by a ‘service navigator’ to ensure their needs are met.

**Methods:**

Using an RCT we will determine: (1) parental engagement with developmental surveillance; (2) access to services for those with mental health and social care needs; and (3) uptake of service recommendations. Three hundred parents/carers of children aged 6 months to 3 years (recruited from a culturally diverse, or rural/regional site) will be randomly allocated to the ‘care-as-usual’ or ‘intervention’ group. A mixed methods implementation evaluation will be completed, with semi-structured interviews to ascertain the acceptability, feasibility and impact of the WMG-E platform and service navigator.

**Conclusions:**

Using WMG-E is expected to: normalise and de-stigmatise mental health and psychosocial screening; increase parental engagement and service use; and result in the early identification and management of child developmental needs, parental mental health, and family psychosocial needs. If effective, digital solutions such as WMG-E to engage and empower parents alongside a service navigator for vulnerable families needing additional support, will have significant practice and policy implications in the pandemic/post pandemic period.

**Trial registration:**

The trial (Protocol No. 1.0, Version 3.1) was registered with ANZCTR (registration number: ACTRN12621000766819) on July 21st, 2021 and reporting of the trial results will be according to recommendations in the CONSORT Statement.

## Background

Due to the COVID-19 pandemic, families, particularly those from disadvantaged backgrounds experienced significant psychosocial stress and mental health challenges [1]. In Australia, for example, despite the low infection rates and consequent adverse social and economic impact, approximately 1.6 million families experienced financial hardship due to COVID-19 associated job losses and financial stress [2], resulting in an extra 780,000 Australian children living in families experiencing employment stress [3, 4]. Further, parental mental health difficulties consequent to the pandemic can adversely impact children’s development and wellbeing [3, 5, 6]. Specifically, families from priority populations such as culturally and linguistically diverse (CALD) as well as from regional and rural communities (i.e., areas that lie beyond the major cities) are particularly likely to experience health care inequality [7, 8]. These risks were intensified by the closure of in-person preventative and health promotion programs, such as child wellbeing checks. This combination of circumstances, substantially reduced access to resources for vulnerable families during the pandemic [9].

When in-person consultations closed, health organizations embraced technology and offered online services to continue providing access to services [10]. Watch Me Grow – Electronic Platform (WMG-E) is an example of one such innovative platform that can help health services reach vulnerable families in their homes, in the community, or during opportunistic contacts (e.g. immunisation) with health professionals such as General Practitioners (GPs) and Child and Family Health Nurses (CFHN) [9]. WMG-E is a web-based application that incorporates the Centre for Disease Control (CDC) “Learn the Signs Act Early (LTSAE)” program which consists of age-appropriate developmental checklists and ‘red flags’ for parental concern of children from birth to 5 years (see measures section for a detailed description of the LTSAE) [11]. In Australia, the New South Wales (NSW) State Government has incorporated the LTSAE program into the *My Personal Health Record Blue Book* developmental surveillance program [12]. Furthermore, translations of the LTSAE are available for the 19 of the most commonly spoken languages in NSW [12]. WMG-E serves as a digital tool to engage and empower parents to actively participate in their children’s developmental monitoring. Parents are provided with anticipatory guidance and automatic reminder emails at the recommended ages and stages for child developmental checks for ongoing developmental monitoring. When parents raise any concerns on the LTSAE red flag items, they are guided to seek more comprehensive assessments by health service providers.

The proposed study will expand WMG-E by incorporating screeners for parents’ mental health and unmet psychosocial needs (e.g., financial support, housing) to optimise families’ wellbeing. Like the developmental screener, when mental health and/or unmet psychosocial risks are indicated, families will be directed to relevant resources electronically through WMG-E in the control group while the intervention group will be guided to receive more detailed assessments and provided ongoing care to ensure the uptake of recommended services. This study also aims to evaluate whether additional support through a ‘service navigator’ (i.e., WMG-E + service navigator) increases family access and uptake of services for families identified as at high-risk by WMG-E. Previous research conducted by Hughes and colleagues [13] has shown that the involvement of a service navigator can enhance families’ connections to services. The role of the service navigator, similar to that of the care coordinator in Hughes et al.’s [13] study, will be to review the parents’ mental health, psychosocial, and developmental screener results, connect them with relevant support services as needed, facilitate access and uptake of recommended services and provide continuity of care to ensure that their needs are met. Specifically, in the intervention group, the navigator will contact the family initially to discuss and clarify the concerns that were raised by the family while completing WMG-E. Once the service navigator has clarified the family’s needs, they will provide guidance to the family on available services and supports in their local area, whom to speak to at relevant agencies, specific questions to ask, and, if necessary, help complete referral forms and where needed directly link them with the service. The service navigator will then contact the family within a 2-week period to determine whether they were able to successfully engage with the available services and supports. The service navigator will continue to contact the family on a biweekly basis to check in regarding their engagement with recommended services and determine whether they have any additional concerns or unmet needs.

A “*virtual care approach*” [14] will be used to focus predominantly on families from priority populations from CALD and rural/regional backgrounds, given the higher risk for health care inequality [7, 8]. As approximately 3.6 billion people use social media, the use of web-based applications has become ubiquitous, including those from priority populations [15]. Therefore, by providing a web-based application which is accessible, affordable, and easy to use we hope to improve access and uptake of screening for mental health, psychosocial needs, and developmental needs in some of the most vulnerable populations in NSW. As for newly arrived immigrants with young children, community linkages with friends, family, and GPs are pivotal [16], we will utilise GPs, play groups, social care agencies, government and non-governmental organisations (NGOs) to engage parents, normalise and de-stigmatise mental health and psychosocial screening, and provide urgent targeted interventions.

## Objectives

The primary objectives of the Randomised Controlled Trial (RCT) component involving families of children aged 6 months to 3 years from CALD, regional and rural communities in NSW are to evaluate: (1) the engagement with developmental surveillance; (2) access to services for those with mental health and social care needs; and (3) uptake of service recommendations. Secondary objectives will include examining (1) the effectiveness of the WMG-E platform in identifying and addressing parental mental health, parental psychosocial and child developmental needs; and (2) whether a service navigator, in addition to the WMG-E platform, increases family wellbeing by facilitating access to relevant services and by providing continuity of care.

The objective of the implementation evaluation is to ascertain the acceptability, feasibility and the impact of the WMG-E platform and service navigator.

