### Randomised controlled trial

Using an RCT methodology we will compare a ‘care-as-usual’ (CaU) group with an intervention group. Both groups will complete parental mental health, psychosocial needs, and child developmental screeners via WMG-E. Furthermore, both groups, if risk is identified, will receive electronic resources guiding them to health services that can be accessed for more detailed assessments.

The intervention group will be provided with ongoing monitoring, via a service navigator, to ensure uptake of recommendations and access to additional support for those identified to be at risk. The service navigator will first triage intervention families based on their level of risk as indicated by the WMG-E platform which screens for developmental, parental mental health, and psychosocial risk. Participants who indicate no developmental concerns on the LTSAE and psychosocial concerns on the WE CARE questionnaire [17] and have scores lower than 20 on the Kessler Psychological Distress (K10) scale [18] will be considered low risk. Participants who indicate one or more developmental and/or psychosocial concerns and/or have scores ranging from 20 to 24 on the K10 will be considered medium risk. Participants who have scores equal to or greater than 25 on the K10 and/or indicate risks of homelessness, domestic violence, loss of electricity, or food insecurity will be considered high risk. Completing the screening tools on the WMG-E platform will take between 10 and 15 min.

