## Methods

### Phase 1: randomised controlled trial

#### Design

The study design is a two (group: intervention versus control) by three (time: baseline [Time 1], post-assessment [Time 2], and follow-up [Time 3]) RCT.

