##### Care-as-usual group

Participants allocated to the CaU will complete Time 1 questionnaires and, if indicated, will also receive a message that their responses to the questionnaires suggest developmental, psychological, and/or psychosocial risk and to seek assistance from local services/organisations. They will then be invited via email to complete Time 2 and Time 3 questionnaires. The control group will not have a service navigator and will not receive continuity of care and support.

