##### Economic analysis

Economic evaluation will assess the cost effectiveness (cost utility) of the intervention against usual care. Costs will include the care coordinator for the intervention group and the costs of completed service referrals for both trial arm. Effectiveness will be measured by converting K-10 scores into utilities using a mapping algorithm that converts scores to EQ-5D values [29]. REML will also be applied to assess significant changes in costs and outcomes. An Incremental Cost Effectiveness Ratio (ICER) will then be generated with values $42,000–$67,000 considered to be cost effective [30]. Implementation costs from roll-out will be estimated, including the eligible population size, the number of service coordinators required and service referrals. Sensitivity analysis will then vary key parameters such as service uptake and a threshold analysis will estimate the minimum service engagement required to maintain cost effectiveness in implementation. A value of information analysis will estimate statistical uncertainty and the potential value from further research to optimize implementation.

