## Discussion

Families from disadvantaged backgrounds face a fragmented health system with financial, social, and structural barriers. Even when services are available, engagement and access to services are compounded by cultural and linguistic barriers as well as geographic challenges. These are exacerbated by the pandemic and the consequent impact on in-person services.

This study will address these challenges by testing the WMG-E web-app as a digital navigation tool to engage parents at home or through opportunistic contacts with health, early childhood education or other community/social care services. Extending earlier research using WMG-E to engage parents in developmental monitoring [35], this study will include parental mental health and psychosocial needs, alongside child developmental needs. Thus, this study will test the acceptability, effectiveness, and cost-effectiveness of WMG-E for families of children aged 6 months to 3 years (inclusive) in a predominantly CALD community and a regional/rural community to increase engagement of families with services and better identification of their needs.

Furthermore, this study will specifically evaluate whether a service navigator will increase family wellbeing by facilitating access to relevant services. Families in the intervention group are expected to experience significantly improved parental mental health, psychosocial wellbeing, and development outcomes compared to the control group. By targeting CALD and rural/regional communities, we will demonstrate the feasibility of the WMG-E for the most vulnerable and disadvantaged families. Following this, the online platform will be ready for national implementation with potential for international adaptation.

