### Impact on policy and practice

If findings provide evidence that engaging parents in mental health, psychosocial, and developmental screening via an electronic platform improves parental engagement and access to services, the study will have significant practice and policy implications for supporting vulnerable families. Moreover, the study will serve to clarify the factors that help and hinder the implementation and sustainability of a digital tool within routine services using opportunistic contacts with families. Specifically, by exploring the five domains of the CFIR (intervention characteristics, inner/outer settings, characteristics of individuals involved in implementation and process [36, 37]), we will ascertain the acceptability and cultural appropriateness of the tool, as well as barriers that hinder adoption. This will generate the evidence needed to evaluate the factors influencing program implementation at scale.

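### Both arms receive WMG-E, so the trial estimates what the service navigator adds and cannot test the platform's own effectiveness or cost-effectiveness, as secondary objective 1 and the Discussion say it will

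*Protocol article*

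**What the plan says.** The protocol article describes the two arms clearly. Under Objectives, Randomised controlled trial: "Both groups will complete parental mental health, psychosocial needs, and child developmental screeners via WMG-E", and "both groups, if risk is identified, will receive electronic resources guiding them to health services". The Intervention group and Care-as-usual group sections each provide an on-screen message when the Time 1 answers indicate risk. The Care-as-usual group section states what separates the arms: "The control group will not have a service navigator and will not receive continuity of care and support". The Design section gives "two (group: intervention versus control) by three (time: baseline [Time 1], post-assessment [Time 2], and follow-up [Time 3]) RCT", and the Randomisation section places allocation after the Time 1 questionnaires.

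The aims go further than this. Secondary objective 1 is to examine "the effectiveness of the WMG-E platform in identifying and addressing parental mental health, parental psychosocial and child developmental needs", listed separately from secondary objective 2, which concerns the navigator on top of the platform. The Discussion states that "this study will test the acceptability, effectiveness, and cost-effectiveness of WMG-E for families" and later that the platform would then be ready for national implementation. The Economic analysis will "assess the cost effectiveness (cost utility) of the intervention against usual care". The Limitations cover lack of blinding and the difficulty of separating the navigator from the services attended. They do not mention that the platform is common to both arms.

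**The concern.** A two-arm trial estimates the effect of whatever differs between its arms. Here that is the navigator package, yet one of the two secondary objectives of the RCT and the main claim of the Discussion concern the component that does not differ. If the wording stands, a positive between-arm result could be cited as evidence for rolling out the platform nationally, although the comparison holds no information on that. The label *care-as-usual* adds to the risk: a reader of the cost-utility result would take the comparator to be ordinary care without WMG-E.

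**Working it through.** The point rests on no figure in the plan, so the check compares what each arm receives with what is to be tested.

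**1. Exposure by arm** (150 families planned per arm)

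| Component | Intervention | Care-as-usual | Section |
|---|---|---|---|
| WMG-E screening at Time 1 | 150 of 150 | 150 of 150 | Randomised controlled trial; Randomisation |
| Risk message, if flagged | yes | yes | Intervention group; Care-as-usual group |
| Electronic resources, if flagged | yes | yes | Randomised controlled trial |
| Navigator triage, contact and fortnightly follow-up | yes | no | Randomised controlled trial; Care-as-usual group |
| In-person assessment and warm hand-over, if high risk | yes | no | Randomised controlled trial |

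Difference in platform exposure: 150/150 − 150/150 = 0. A larger sample does not change it.

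**2. What the contrast estimates.** Let P = 1 if a family has the platform and N = 1 if it has the navigator. On the scale of the model, write the mean outcome as

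m(P, N) = a + bP + cN + dPN.

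- Intervention: m(1, 1) = a + b + c + d
- Care-as-usual: m(1, 0) = a + b
- Difference: c + d, the effect of adding the navigator where WMG-E is already in use.

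The platform effect, m(1, 0) − m(0, 0) = b, drops out. Estimating it needs families with P = 0, and there are none.

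**3. The cost-utility ratio.** With costs C and effects E, the trial gives

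ICER = [C(1, 1) − C(1, 0)] / [E(1, 1) − E(1, 0)].

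Platform costs and effects common to both arms cancel. That is correct for the navigator increment, but says nothing on WMG-E against no WMG-E.

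**4. Stated aims against the contrast**

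- Secondary objective 2 and both hypotheses (better access and engagement in the first 6 months; greater gain in wellbeing at 12 months) concern the navigator. They match c + d.
- Secondary objective 1 has two parts. Identifying needs is screening yield, which can be described without a control. Addressing needs, read as an effect, requires b.
- The Discussion's acceptability claim is served by the interviews. Its effectiveness and cost-effectiveness claims for WMG-E require b and an ICER against no platform.

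**5. Could change over time stand in for a control?** No. Families are flagged because of high scores, so regression to the mean is expected. Children grow older and the LTSAE form changes with age. Pandemic conditions may shift over follow-up. Change from Time 1 can be described but not attributed to the platform.

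**The case against.** The strongest reply is that the true contrast is disclosed several times. The Abstract, the Background, secondary objective 2 and both hypotheses all present the navigator as the addition under test, and no model claims a comparison with no platform. Secondary objective 1 is only to be examined. This stands as far as it goes: the design is sound for the navigator question, and screening yield and acceptability need no control. It does not rescue the Discussion, which says in plain terms that effectiveness and cost-effectiveness of WMG-E will be tested, or the part of secondary objective 1 about addressing needs.

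The other side is right on several stronger readings that a reader might infer:

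- *That the economic analysis claims to evaluate the platform.* It does not. The arm-specific cost it names is the care coordinator, which is already the navigator increment; shared costs properly cancel, and the cost list is not stated to be exhaustive. Its fault is the label in "assess the cost effectiveness (cost utility) of the intervention against usual care".
- *That primary objective 1, engagement with developmental surveillance, has no valid between-arm test.* It is not worded as a platform effect. Both arms have the same access to WMG-E, but fortnightly navigator contact could change later engagement, so a comparison is legitimate.
- *That engagement has no measure or model.* A condensed article may leave this to the full protocol or the analysis plan.
- *That the Abstract's conclusions and the policy section assert a platform effect.* The Abstract speaks of expectation and of what follows if effective, alongside a navigator. In the policy section, "engaging parents in mental health, psychosocial, and developmental screening via an electronic platform improves parental engagement and access to services" sits inside a condition. These need aligning; they are not false statements of result.

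**Conclusion.** The point holds for secondary objective 1, in so far as it claims an effect of the platform, and for the Discussion's statement on effectiveness and cost-effectiveness. None of the 300 families is randomised to no platform, so the controlled information on the platform effect is nil, whatever the sample size or analysis model. What the trial can estimate is the effect of adding the navigator package to WMG-E. This follows from the arm descriptions alone and needs no numerical assumption. It should be corrected because it changes what the trial can conclude, but the fault lies in the claims and not in the conduct.

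Two further inferences are not supported. Reducing the three primary objectives to one does not follow from this argument. Nor do the documents show that the power claim fails because controls receive WMG-E. The stated power of over 99% reproduces (0.998 for 30% against 60% with 122 per arm, two-sided 5% assumed). A control rate raised by the platform would lower it: with the intervention held at 60% and 150 per arm, power would be 0.94 at an assumed 40% and 0.41 at an assumed 50%. But the documents give no control rate under WMG-E, so this is a sensitivity and not a finding.

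**What to change.** 1. **Objectives:** restate secondary objective 1 as a descriptive aim, namely screening yield and uptake of WMG-E across both arms, with no causal claim.
2. **Discussion:** say that the trial tests the effectiveness and cost-effectiveness of adding a service navigator to WMG-E, with acceptability of the platform assessed descriptively. Do not rest readiness for national roll-out of the platform on the between-arm result.
3. **Randomised controlled trial, Care-as-usual group and Economic analysis:** label the comparator *WMG-E alone*, so that the ICER is read as WMG-E plus navigator against WMG-E alone.
4. **Abstract conclusions, Impact on policy and practice, and Limitations:** align the first two with items 1 and 2, and add to the Limitations that both arms share the platform.

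Leave the three primary objectives in place. Engagement with surveillance may still be compared between arms as a navigator effect.

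The cost is wording in the protocol and wherever the same statements are repeated. Recruitment, allocation, outcomes, models and sample size stay as they are. The downside is a narrower headline claim.
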